### Sample size calculation

The sample size calculation is based on the primary endpoint “CCI within 30 days after the index operation”. Assumptions are based on the literature [39, 40, 50]: a decrease of the CCI by 10 points is considered relevant by patients and clinicians (minimal important difference, [40]) and a conservative standard deviation of 20 is assumed. The CCI in major abdominal surgery (control intervention) is assumed to be 22 [39, 40]. We hypothesise to decrease the CCI by 10 points in the interventional group (minimal important difference, [40]). The primary endpoint is tested simultaneously using a two-sided *t* test in the subgroup of patients with a minimally invasive surgery and the subgroup of patients experiencing an open surgery. The ratio of minimally invasive to open is expected to be 1:1. Therefore, the overall two-sided significance level of α = 0.05 is adjusted by Bonferroni correction, yielding α = 0.025 for each of the two subgroups. Thus, to achieve a power of 80%, a sample size of *n* = 156 (78 per group) has to be recruited per subgroup with a total required sample size of the trial of *n* = 312 (156 per therapy group). To compensate for drop-outs and lost-to-follow-ups, a further 10% of patients will be randomised, leading to a total sample size of *n* = 348 (174 per group). Patients who die during the observation period receive the maximum number of 100 CCI points per definition [39, 40].

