### Statistical analysis

For the examination of the primary endpoint “CCI within 30 days after the index operation”, the hypotheses to be assessed for each subgroup (minimally invasive or open) in the primary analysis are as follows: H0: μ1 = μ2 vs. H1: μ1 ≠ μ2, where μ1 and μ2 denote the mean CCI in the control and the intervention group respectively. The significance level is set to a two-sided α = 0.025 per subgroup test. Due to the stratified randomisation and relatively large number of centres in relation to the sample size, inclusion of centre as a random effect is recommended [51]. Therefore, the primary endpoint will be examined in the respective subgroup (minimally invasive or open) using a linear mixed model including centre as random intercept and group as fixed effect, which leads to equal or even increased power as compared to using a conventional two-sided *t* test [52].

The primary analysis will be conducted based on the full analysis set according to the intention-to-treat (ITT) principle and comprises all patients in the group they were randomised to. In the ITT analysis, missing data for the primary outcome variable will be replaced by using multiple imputation, which takes the covariates treatment group and centre into account by application of the fully conditional specification method [53]. The per protocol (PP) set consists of all patients treated per protocol; no missing data will be imputed. An additional mobility population consists of all patients who were randomised, had no re-operation within 30 days and had not been on the intensive or intermediate care ward for ≥ 4 days during the first postoperative week.

In general, for the full analysis set, all baseline values and secondary outcomes will be evaluated descriptively, and descriptive *p* values are reported together with 95% confidence intervals for the corresponding effects. Thereby, secondary endpoints will be evaluated descriptively using regression models including group as fixed effect and centre as random intercept as specified for the primary endpoint.

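### The fixed Bonferroni split between the two surgery subgroups is valid, but Holm's procedure would give more power at the same family-wise 5% and at almost no cost

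*Protocol article*

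**What the plan says.** In the Protocol article, the Sample size calculation section tests the CCI within 30 days simultaneously in two disjoint sets of patients: "the subgroup of patients with a minimally invasive surgery and the subgroup of patients experiencing an open surgery". For this, the two-sided 0.05 for the whole trial "is adjusted by Bonferroni correction, yielding" 0.025 in each subgroup. The planning values are one treatment effect ("We hypothesise to decrease the CCI by 10 points in the interventional group") and one spread ("a conservative standard deviation of 20 is assumed"). They lead to 78 per treatment group in each subgroup, 312 in total, and 348 after a 10% allowance for drop-out.

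The Statistical analysis section confirms the rule for the primary analysis: "The significance level is set to a two-sided α = 0.025 per subgroup test". Neither section has a step-down, step-up or alpha-recycling rule. Neither says whether the trial counts as positive only when both subgroups are significant.

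**The concern.** Under the rule as written, a subgroup with a p-value between 0.025 and 0.05 is declared negative even if the other subgroup is clearly positive. Holm's procedure would then test the second subgroup at 0.05, with the same strong control of the family-wise error at 5%. It rejects everything Bonferroni rejects and sometimes more, whatever the dependence between the tests.

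The article fixes the per-test level in two places, so this is a stated choice and not a detail left to the statistical analysis plan. The planning scenario is a 10-point benefit with no distinction between subgroups, and this is where the difference between the procedures is largest. One practical risk is an apparent contrast between laparoscopic and open surgery that reflects only the decision rule. The Discussion names this same distinction as one along which future studies might refine step goals.

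**Working it through.** **Inputs** (Sample size calculation): difference 10, SD 20, two-sided 0.025 per subgroup, 80% power, two subgroups in an expected 1:1 ratio, 10% drop-out. Allocation is 1:1 (Abstract, Methods).

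**The plan's own figure.** The normal approximation gives 77 per group. The exact noncentral t gives power 79.8% at 77 and 80.4% at 78, so 78 is the smallest sufficient n. Then 4 × 78 = 312. With drop-out, 78 / 0.9 = 86.7, rounded up to 87, and 4 × 87 = 348. The stated numbers reproduce.

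**Building blocks at 78 per arm, true difference 10.** Power is a = 0.8039 at 0.025 and b = 0.8735 at 0.05, so b − a = 0.0696. The two tests are treated as independent because the subgroups contain different patients.

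**Formulas with the same effect in both subgroups**
- Bonferroni: per subgroup a; both a² = 0.8039² = 0.646.
- Holm: per subgroup a + (b − a)a = 0.8039 + 0.0696 × 0.8039 = 0.860; both b² − (b − a)² = 0.7630 − 0.0048 = 0.758.
- Hochberg: per subgroup a + (b − a)b = 0.8039 + 0.0696 × 0.8735 = 0.865; both b² = 0.763.
- At least one: Bonferroni and Holm 1 − (1 − a)² = 0.962; Hochberg adds (b − a)², giving 0.966.

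| 10 points in both | Bonferroni | Holm | Hochberg |
|---|---|---|---|
| Power per subgroup | 80.4% | 86.0% | 86.5% |
| Both subgroups | 64.6% | 75.8% | 76.3% |
| At least one | 96.2% | 96.2% | 96.6% |
| Family-wise error, no effect in either | 4.94% | 4.94% | 5.00% |

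The last row is 1 − 0.975² = 0.0494 for Bonferroni and Holm; Hochberg adds 0.025² = 0.0006. A simulation with 200,000 replicates agrees with the Holm and Hochberg columns.

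Holm confirms both where Bonferroni confirms one with probability 2a(b − a) = 2 × 0.8039 × 0.0696 = 0.112, about one trial in nine. In terms of sample size, Holm reaches 80% per subgroup with 68 per group and Hochberg with 67, against 78.

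**Unequal effects, 78 per arm.** Each subgroup's gain is its own (b − a) multiplied by the other subgroup's power, taken at 0.025 for Holm and at 0.05 for Hochberg.

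| True differences | Bonferroni | Holm | Hochberg |
|---|---|---|---|
| 10 and 5 points | 80.4% / 24.4% | 82.1% / 32.3% | 82.8% / 32.9% |
| 10 and 0 points | 80.4% / 2.5% | 80.6% / 4.5% | 80.7% / 4.7% |

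In the second row, the figure after the slash is the false-positive rate in the null subgroup: 0.025 + 0.025 × 0.8039 = 0.045 for Holm and 0.025 + 0.025 × 0.8735 = 0.047 for Hochberg. That is the whole family-wise error in this scenario, and it stays below 5%.

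**The case against.** The strongest reply is that nothing in the plan is wrong. Bonferroni is valid, the two sections agree, and the sample size was built for it and delivers 80.4% in each subgroup. All of this stands. A reader might infer that the split is a mistake or leaves the trial underpowered; the documents do not support that.

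A reader might also infer that Bonferroni buys nothing in return. That goes too far. It holds the error in a single null subgroup at 2.5%, where Holm lets it rise to about 4.5% if the other subgroup has the full effect. It keeps each subgroup's verdict independent of the other's data, and it pairs with simple 97.5% confidence intervals. These are real but small advantages. The article gives none of them as its reason, and it sets the family-wise 5% as the error to be controlled.

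Third, the gain depends on both subgroups benefiting, and the article itself gives grounds for doubt. Its Discussion cites a single-centre trial of trackers with a step goal in which step counts rose after laparoscopic but not after open surgery. The unequal-effect figures therefore belong beside the headline gain. It would also be wrong to read 64.6% as the trial's chance of success, because the article does not require both subgroups to be positive. For at least one, Holm changes nothing.

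Finally, this is more than a sentence in the analysis plan. It changes the primary decision rule of an open-label trial that had included 219 of 348 patients at 31 January 2020, so it needs a documented amendment with a reason. That affects how the change is made, not whether it is worthwhile.

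**Conclusion.** The point holds as a missed efficiency. At the same family-wise two-sided 5%, the fixed 0.025 per subgroup is uniformly less powerful than Holm. Under the article's planning assumptions the loss is 5.6 percentage points per subgroup (86.0 − 80.4) and 11.2 points for confirming both (75.8 − 64.6). It is close to nothing for the effective subgroup if only one subgroup benefits, and nothing for at least one positive result. No error rate is inflated and no stated power target is missed.

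The figures assume t tests with SD 20, 78 evaluable patients per arm and subgroup, and independent tests. The mixed model with centre as random intercept may shift them slightly. Holm's error control does not need independence. Hochberg is acceptable because the subgroups are disjoint patient sets that share only centres.

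**What to change.** In the Sample size calculation and Statistical analysis sections, replace the fixed level with wording such as: the two subgroup hypotheses are tested by Holm's procedure at a family-wise two-sided 0.05; the smaller p-value is compared with 0.025 and, if significant, the larger with 0.05. Hochberg is an acceptable alternative, but name one procedure only. Keep n = 312/348, and state 80% as the minimum power per subgroup. Carry the rule into the statistical analysis plan.

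Make the change before database closure and record that it was made without sight of the data. The article allows this: the analysis plan is to be written before closure, and the biometricians get database access only afterwards. The cost is a short, reasoned protocol amendment; no patients, visits or data items are added. Acknowledge two small downsides: the higher error rate in a null subgroup (about 4.5% instead of 2.5% when the other has the full effect), and 97.5% intervals that no longer match the decision rule exactly, although they can still be reported.

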### Statistical analysis

For the examination of the primary endpoint “CCI within 30 days after the index operation”, the hypotheses to be assessed for each subgroup (minimally invasive or open) in the primary analysis are as follows: H0: μ1 = μ2 vs. H1: μ1 ≠ μ2, where μ1 and μ2 denote the mean CCI in the control and the intervention group respectively. The significance level is set to a two-sided α = 0.025 per subgroup test. Due to the stratified randomisation and relatively large number of centres in relation to the sample size, inclusion of centre as a random effect is recommended [51]. Therefore, the primary endpoint will be examined in the respective subgroup (minimally invasive or open) using a linear mixed model including centre as random intercept and group as fixed effect, which leads to equal or even increased power as compared to using a conventional two-sided *t* test [52].

The primary analysis will be conducted based on the full analysis set according to the intention-to-treat (ITT) principle and comprises all patients in the group they were randomised to. In the ITT analysis, missing data for the primary outcome variable will be replaced by using multiple imputation, which takes the covariates treatment group and centre into account by application of the fully conditional specification method [53]. The per protocol (PP) set consists of all patients treated per protocol; no missing data will be imputed. An additional mobility population consists of all patients who were randomised, had no re-operation within 30 days and had not been on the intensive or intermediate care ward for ≥ 4 days during the first postoperative week.

In general, for the full analysis set, all baseline values and secondary outcomes will be evaluated descriptively, and descriptive *p* values are reported together with 95% confidence intervals for the corresponding effects. Thereby, secondary endpoints will be evaluated descriptively using regression models including group as fixed effect and centre as random intercept as specified for the primary endpoint.

In further exploratory analyses, the association of variables with the primary and secondary outcomes will be assessed. In addition, subgroup analyses will be carried out. The safety analysis includes calculation of frequencies and rates of complications together with 95% confidence intervals. All analyses will be done using SAS version 9.4 or higher. The analyses will be described in further detail in the statistical analysis plan, which will be written before database closure.

It is planned to make all trial data publicly available after the publication of trial results.

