### Visit 1 (preoperative, informed consent)

All consecutive patients are screened for potential inclusion. Eligible patients are asked for informed consent. Enrolled patients are instructed on how to use the wearable FT (see “Intervention”). In addition, the following data items will be collected: (1) demographic data; (2) baseline data; (3) medical history/comorbidities; (4) HRQoL (EORTC QLQ-C30) [44]; (5) baseline functional data via the QoR-15 questionnaire [41, 42]; (6) status of physical activity via the Duke Activity Status Index (DASI) [49].

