### Visit 2 (day of surgery, postoperative day 0)

On the day of surgery, data concerning the performed procedure are collected, including duration of surgery, blood loss, type of surgery and type of surgical access (open vs. laparoscopic). Furthermore, data regarding number and types of abdominal drains, nasogastric tubes, urinary catheters and postoperative analgesic are collected. At this time, randomisation will be performed (see above) and the wearable FT is attached.

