### Risk of bias

In order to ensure that both treatment groups are well balanced for known and unknown confounders, the assignment to the two groups is based on randomisation. In order to document potential selection bias, all consecutive screened patients are listed in a screening list. To exclude the quality of surgery as a key factor for postoperative complications, randomisation is performed at the time of skin closure or later. In order to standardise outcome assessment, medical students are trained during a clinical investigator training (CIT) course in study-specific procedures as well as good clinical practice to reduce detection bias. The curriculum of the CIT has been described elsewhere [36]. Furthermore, obligatory online training material is available to all participating students. In addition, medical students are supported by surgeons experienced in clinical trials (clinician scientists) at their local sites. Blinding, however, is impractical in our study setting, as it would require ornate blinding methods, which contradict the pragmatic trial design. However, in order to counteract the risk of bias introduced by the unblinded study design, we have chosen a primary endpoint robust against unconscious or intentional influence, namely the Comprehensive Complication Index (CCI). The Dindo-Clavien complication classification, on which the CCI is based, is an objective outcome measure, as it grades complications according to their sequelae (e.g. death, re-operation, re-intervention, etc.) and can hardly be influenced by subjective impressions. However, this does not hold true for some of the secondary outcomes, e.g. patient-reported measures like pain. Furthermore, follow-up is limited to 30 days; thus, few missing values are expected. Since patients are still hospitalised for parts of this period, the attrition bias is expected to be low.

In addition, known courses for postoperative recovery will be meticulously recorded during follow-up in order to record potential confounders. These include the preoperative physical fitness (assessed via the DASI score), the impact of surgery (laparoscopic vs. open), the type of recovery programme, analgesic regime, duration of catheter, drain and tube placement and the degree of physiotherapy.

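### The primary CCI model contains only group and centre within each access subgroup, so precision available from pre-randomisation patient data already collected goes unused

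*Protocol article*

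**What the plan says.** All references are to the protocol article.

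- **Primary model (Statistical analysis).** The CCI within 30 days is analysed separately in the minimally invasive and the open subgroup, "using a linear mixed model including centre as random intercept and group as fixed effect". No other term is named. The multiple imputation of missing CCI values uses treatment group and centre.
- **Test and size (Sample size calculation).** "The primary endpoint is tested simultaneously using a two-sided" *t* test in the two subgroups, with Bonferroni correction "yielding α = 0.025 for each of the two subgroups". The difference is set at 10 points, because "a decrease of the CCI by 10 points is considered relevant by patients and clinicians", and the SD at 20.
- **Data available before allocation.** Visit 1 collects demographics, comorbidity, quality-of-life and recovery scores, and "status of physical activity via the Duke Activity Status Index (DASI"). Visit 2 collects "duration of surgery, blood loss, type of surgery and type of surgical access (open vs. laparoscopic"). According to Assignment of intervention and randomisation, allocation takes place on the day of surgery and not before the skin is closed.
- **Confounder list (Risk of bias).** Potential confounders are to be recorded during follow-up. The list starts with preoperative fitness (DASI) and surgical access and continues with "the type of recovery programme, analgesic regime, duration of catheter, drain and tube placement and the degree of physiotherapy".
- **Other use of covariates (Statistical analysis).** Exploratory analyses will look at associations of variables with the outcomes. Their models are not given, and further detail is left to a statistical analysis plan.

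**The concern.** Late randomisation gives this trial an unusually rich baseline. Not only the patient's fitness and history but also the operation itself is fixed before the arm is assigned. These facts can plausibly predict complications, and eligibility is wide: any elective abdominal operation expected to exceed two hours or 500 ml of blood loss, with no restriction by organ. Splitting by access leaves the remaining differences between patients and procedures inside each comparison of 78 against 78.

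In a linear model, adjustment for such variables leaves the target, the mean difference in CCI, unchanged and shrinks its standard error. The article accepts this kind of reasoning for centre, whose random intercept it defends partly on grounds of power, but does not extend it to patient characteristics. At stake is a wider confidence interval than the collected data require, in two tests that each have little power to spare.

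The second, smaller matter is vocabulary. How long catheters, drains and tubes stay in and how much physiotherapy is given are determined after allocation. They can be affected by the mobilisation programme or by the complications being counted. They cannot confound a randomised comparison, and calling them confounders could lead an analyst to adjust the treatment effect for them.

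**Working it through.** **Inputs from the article:** difference 10 (control 22, intervention 12); SD 20; two-sided α = 0.025 per subgroup; power 80%; allocation 1:1; 10% drop-out.

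**Assumed input:** R², the share of CCI variance within a subgroup that is explained by baseline covariates. The article gives no value; 0.05 to 0.30 is used as a range.

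**Step 1. Reproduce the planned size.**
- Normal approximation: n per arm = 2 × (z₀.₉₈₇₅ + z₀.₈₀)² × (20/10)² = 2 × (2.241 + 0.842)² × 4 ≈ 76.04, so 77.
- Exact two-sided *t* test (noncentral *t*, df = 2n − 2, noncentrality = 10 / (20 × √(2/n))): power is 0.798 at n = 77 and 0.804 at n = 78. Hence 78 per arm, 156 per subgroup and 312 in total, as stated.
- Drop-out: 156 / 0.9 = 173.3, so 174 per therapy group and 348 in total, as stated.

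The planned size is reproduced, and it rests on an unadjusted SD of 20.

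**Step 2. Effect of adjustment.** Replace the SD by 20 × √(1 − R²) and keep 78 per arm and α = 0.025. The few degrees of freedom spent on covariates are ignored.

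| Assumed R² | Residual SD | Exact power at 78 per arm | n per arm for 80% (normal approx.) | Difference detectable with 80% power at 78 per arm (normal approx.) |
|---|---|---|---|---|
| 0 | 20.00 | 80.4% | 77 | 9.87 |
| 0.05 | 19.49 | 82.5% | 73 | 9.62 |
| 0.10 | 18.97 | 84.7% | 69 | 9.37 |
| 0.20 | 17.89 | 88.9% | 61 | 8.83 |
| 0.30 | 16.73 | 92.8% | 54 | 8.26 |

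The gain runs from 82.5 − 80.4 = 2.1 to 92.8 − 80.4 = 12.4 percentage points per subgroup test. In terms of patients, the variance falls by the factor 1 − R². An R² of 0.20 is therefore worth 1 / 0.80 = 1.25 times the sample.

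**Step 3. Sort the variables by time of origin.**
- Fixed before allocation: DASI, demographics, comorbidity, type of operation, length of operation, blood loss, surgical access.
- Arising after allocation: duration of catheters, drains and tubes; amount of physiotherapy. The visit schedule (Table 1) follows these through the postoperative visits.
- Not clear from the text: recovery programme and analgesic regime, which may be set before allocation.

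The Risk of bias section puts all three kinds under one label.

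**The case against.** The strongest reply is that leaving out covariates is a legitimate choice. The trial was sized for an unadjusted test, the model matches that sizing, and the planned power is delivered. The SD of 20, which the article calls conservative, already contains the variation between procedures. All of this stands. A reader might infer that the primary analysis is biased or underpowered; the documents support neither.

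A reader might also infer that no pre-randomisation factor is taken into account. That is too strong: access is conditioned on through the separate subgroup tests, and centre is in the model.

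The size of the gain follows from an assumed R², so the power figures show what could be had, not what will be had. The breadth of case mix is read from the eligibility criteria. The procedures named in the Background are those of other trials and are not this trial's stated mix.

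One might say that covariates belong in the unseen analysis plan. Supplementary adjusted analyses may well be there. The primary model, however, is written out in the article and can be judged as written.

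On the confounder list, a tempting reading is that the protocol will adjust the treatment effect for physiotherapy or drain duration. It nowhere says so. The items are to be recorded, which is sensible in an unblinded trial, and the exploratory analyses concern associations with outcome. Only the label is at fault.

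**Conclusion.** The point holds as a matter of efficiency. Within each access subgroup the primary model uses no patient-level prognostic covariate, although several are available and fixed before allocation. Validity, α and the stated 80% power are intact. The forgone gain is about 2 to 12 percentage points of power per subgroup test if baseline factors explain 5% to 30% of CCI variance. That range is an assumption, and the calculation also presumes roughly linear covariate effects and the planned 78 evaluable patients per arm. If R² is near zero, almost nothing is gained, and little is lost with a short covariate list.

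The confounder wording is a minor correction with no effect on the primary result as planned.

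**What to change.** 1. Before database closure, and without sight of outcomes by arm, add a short fixed list of pre-randomisation covariates to the primary mixed model in each subgroup, for example DASI, age and procedure group. State the coding of each, including the procedure groups.
2. Keep the group-plus-centre model as a sensitivity analysis.
3. Add the same covariates to the imputation model for missing CCI values, so that the imputation and analysis models agree.
4. In the Risk of bias section, separate baseline covariates (DASI, surgical access) from care variables that arise after allocation (catheter, drain and tube duration, physiotherapy). Say that the latter are described by arm and not adjusted for when the treatment effect is estimated. State when recovery programme and analgesic regime are set.

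The cost is small but not nil. A published primary model would be amended during recruitment: the Trial status section reports 219 of the planned 348 patients included by 31 January 2020. The change therefore has to be dated and documented as made blind to outcomes by arm. A few missing baseline values will need a simple stated rule. If operating time or blood loss were used, it should be confirmed that they are recorded before the arm is known, because the article says only that both belong to visit 2. No new data and no change to the sample size are needed.

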### Visits 3–6 (postoperative days 2, 4, 6 and 8 (± 1 day))

Visits 3–6 have equivalent contents with the exception of the QoR-15 questionnaire, which is only administered at visit 4, the 6-MWT, which is performed only at visit 5 (or at discharge, whichever comes first) and HRQoL assessment (EORTC QLQ-C30), which is only performed at visit 6. If the patient is discharged before undergoing visits 3–6, the respective visits are skipped and the discharge visit (visit 7) is performed.

Visits 3–6 include assessment of postoperative complications according to Dindo-Clavien (primary endpoint). In addition, all secondary endpoints will be assessed. Furthermore, data on physiotherapy and mobilisation support by health-care team members other than physiotherapists (e.g. nursing staff) are collected. Finally, patients in the experimental group receive instructions about their step goals, and it is assessed whether these mobilisation targets have been met since the last visit.

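### The imputation model named for the primary endpoint leaves out surgery type and the complications already recorded; any bias is conditional and small, and the remedy needs no new data

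*Protocol article*

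**What the plan says.** The Statistical analysis section of the protocol article makes two tests confirmatory, one per surgery type: "the primary endpoint will be examined in the respective subgroup (minimally invasive or open) using a linear mixed model including centre as random intercept". The Sample size calculation section splits the significance level accordingly: "adjusted by Bonferroni correction, yielding α = 0.025 for each of the two subgroups".

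For the intention-to-treat analysis, missing values of the primary outcome are handled by "multiple imputation, which takes the covariates treatment group and centre into account by application of the fully conditional specification method". Treatment group and centre are the only covariates named there. The text does not say whether imputation is run within each surgery type or over all patients together.

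Two further pieces of information are available. Surgery type is the randomisation stratum and is fixed at skin closure or later, so it is known for every randomised patient. Complications are also recorded well before day 30: "Visits 3–6 include assessment of postoperative complications according to Dindo-Clavien (primary endpoint"; Table 1 adds assessments at discharge and at day 30.

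**The concern.** An imputation model should contain at least what the analysis model conditions on. Here each primary model conditions on surgery type because it is fitted within one surgery type. If imputation ignores surgery type, a missing value in an open-surgery patient is drawn partly from minimally invasive patients, and the reverse. If the treatment effect differs by surgery type, the two estimates are pulled towards each other, which blurs the contrast that the two separate tests are meant to show.

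The second omission concerns observed data. The Outcome measures section describes the CCI as a summary of all of a patient's complications, so on that description a later complication cannot lower it. A patient lost after discharge therefore has a known minimum. A draw based on group and centre alone can fall below it, for example for a patient with a documented re-operation. It also makes the missing-at-random assumption harder to defend, because dropout after a complicated course can then depend on data that the model does not see. The trial is unblinded and patients may withdraw at any time, so such dropout could differ by arm.

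**Working it through.** **The plan's own figure.** "We hypothesise to decrease the CCI by 10 points in the interventional group" and "a conservative standard deviation of 20 is assumed"; two-sided α is 0.025 per subgroup and power is 80%. The normal approximation gives 77 per arm. The exact t test gives 77.3, rounded up to 78, with power 0.804. Then 4 × 78 = 312, 156/0.9 = 173.3, rounded up to 174 per therapy group, and 348 in total. The figures reproduce, and this point does not change them. The planned standard error of a stratum effect is 20 × √(2/78) = 3.2.

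**Leaving out surgery type.** Define the effect as control minus intervention. Let m be the missing fraction in an arm, μ the stratum mean in that arm, and P the arm mean pooled over strata (1:1 split, as the plan expects). If imputation ignores surgery type, then

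bias in a stratum = m(control) × [P(control) − μ(control)] − m(intervention) × [P(intervention) − μ(intervention)].

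The plan gives one control mean, 22, and one 10% dropout allowance. All stratum-specific means and arm-specific missing fractions below are assumptions.

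1. Plan's assumptions, 22 vs 12 in both strata, 10% missing in both arms: pooled and stratum means coincide, so the bias is 0 and 0.
2. Means 17 vs 7 (minimally invasive) and 27 vs 17 (open), effect 10 in both, 10% missing. Minimally invasive: 0.10 × 5 − 0.10 × 5 = 0. Open: −0.5 + 0.5 = 0.
3. Means as in 2, missing 5% in control and 15% in intervention. Minimally invasive: 0.05 × 5 − 0.15 × 5 = −0.5. Open: +0.5.
4. Means 16 vs 6 and 28 vs 28 (true effects 10 and 0), 10% missing in both arms; pooled means are 22 and 17. Minimally invasive: 0.10 × 6 − 0.10 × 11 = −0.5, estimate 9.5. Open: −0.6 + 1.1 = +0.5, estimate 0.5. The bias scales with missingness: 0.25 at 5% and 1.0 at 20%.
5. Means as in 4, missing 5% in control and 15% in intervention. Minimally invasive: 0.05 × 6 − 0.15 × 11 = −1.35, estimate 8.65. Open: −0.3 + 1.65 = +1.35, estimate 1.35.

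**A main effect of surgery type is not enough.** In scenario 4 an additive model (group plus surgery type) imputes the average effect of 5 in both strata. The estimates are 0.9 × 10 + 0.1 × 5 = 9.5 and 0.9 × 0 + 0.1 × 5 = 0.5, unchanged. The interaction with group, or imputation within stratum, is needed.

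**Leaving out recorded complications.** Assume effect 10 in both strata, SD 20, and a correlation of 0.8 between an early complication score and the final score. In the intervention arm 17% are missing above the average early score and 3% below it. In control 10% are missing at random.

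- The mean of a standard normal score above zero is √(2/π) = 0.798.
- Mean early score of missing intervention patients: 0.798 × (0.085 − 0.015)/0.10 = 0.559.
- Mean early score of observed intervention patients: 0.798 × (0.415 − 0.485)/0.90 = −0.062.
- Bias: 0.10 × 0.8 × 20 × (0.559 + 0.062) = 0.99 points in favour of the intervention, in both strata.
- With the same dependence in both arms the shifts cancel and the bias in the effect is 0.

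**Simulation check** (348 patients, 15 centres, 600 runs; biases for minimally invasive and open, Monte Carlo error about 0.05):

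- Effects 10 and 0, 10% missing: −0.55 and +0.51 with group and centre; −0.01 and +0.05 after adding surgery type and its interaction with group.
- Complication-related dropout in the intervention arm only: +1.05 and +1.01 with group and centre; +1.01 and +1.00 after adding surgery type and its interaction; +0.02 and +0.02 once the early score is added as well.

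**The case against.** The strongest reply is that the text does not say only these covariates, and does not say that imputation is pooled over strata. Group and centre are exactly the terms of the mixed model fitted within each surgery type, so imputation within surgery type is a natural reading. On that reading the first omission disappears. The article also leaves further detail to the analysis plan. This is fair, and it is why the surgery-type part holds only for the literal reading. It does not dispose of the second part: imputation within stratum on group and centre still ignores recorded complications.

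It can also be said that the article does not define when a CCI counts as missing, that the last visit is also foreseen at premature termination with a complication assessment, and that deaths are scored 100. These would reduce the number of imputed values. They do not tell the imputation model to use what was recorded for a patient who is still imputed.

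Three stronger readings are tempting and are not supported:

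- A reader might infer that both stratum effects are biased in any event. Scenarios 1 and 2 give zero.
- A reader might take the earlier single-centre trial cited in the Discussion, with more steps after laparoscopic but not after open surgery, as evidence that the CCI effect differs. It concerns step counts and makes a difference only plausible.
- A reader might object that imputed CCI values would be negative, in about 14% of draws at mean 22 and 27% at mean 12 with SD 20. That presumes normal draws. The plan names only fully conditional specification, which also allows predictive mean matching.

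Finally, the Risk of bias section expects few missing values. The 10% is a sample-size allowance, so the sizes above may overstate what occurs.

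**Conclusion.** The point stands in limited form. The plan names an imputation model for its confirmatory endpoint that omits the variable defining the two primary tests and omits observed data that set a floor for the outcome. That is a stated choice, and an analysis plan that followed the sentence literally would carry it forward.

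Against the standard error of 3.2, the assumed departures amount to roughly 0.16 (0.5 points), 0.31 (1 point) and 0.42 (1.35 points) standard errors. None of these would by itself overturn a true 10-point effect. The possibility of imputing a value below what is documented does not depend on these averages, and is reason enough to amend the model. Severity is minor to moderate; it is not a defect that must be repaired before the trial can be interpreted.

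**What to change.** State the following in the analysis plan before database closure:

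- Imputation is run separately within each surgery-type stratum, or in one model with surgery type and its interaction with treatment group. A main effect alone does not suffice when effects differ.
- The CCI from complications recorded up to last contact is a predictor.
- The imputed 30-day CCI lies between that value and 100. One way is predictive mean matching on the increment after last contact: observed increments are never negative, so the floor holds, and the sum is capped at 100.

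The cost is a sentence or two of text and slightly more analysis work. No new data and no change in sample size are needed. The one practical drawback is sparse centres within strata: 174 patients per stratum over 15 centres is about 11.6 per centre, or 5.8 per arm. If that makes imputation within strata unstable, the single model with the interaction is the alternative.
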